### 2.5. Procedures and Outcomes

The procedures in this study will be conducted by trained professionals affiliated with the multidisciplinary team at each study center. After agreeing to participate and signing the Informed Consent Form (ICF) (Supplementary Materials S1), participants will undergo a baseline assessment (Figure 3).

A standardized evaluation form will be used for data collection on identification, characterization, and verification of inclusion and exclusion criteria. This evaluation form will include data related to anthropometric assessment (weight, height, body mass index), clinical assessment (diagnosis, type of ALS, symptoms, medications in use), use of non-invasive ventilation (NIV), and engagement in respiratory and motor physiotherapy and its frequency, in addition to monitoring of vital signs [heart rate (HR), systemic blood pressure (BP), and peripheral oxygen saturation (SpO_2_)].

Next, electrodes and sensors will be placed on the muscles to be analyzed, both for electromyography and for functional spectroscopy. Patients will undergo evaluations of pulmonary function, Peak Cough Flow (PCF), Maximum Inspiratory Pressure (MIP), Maximum Expiratory Pressure (MEP), Sniff Nasal Inspiratory Pressure (SNIP), and Sniff Nasal Expiratory Pressure (SNEP). During the execution of the respiratory muscle strength curves, cerebral perfusion [functional near-infrared spectroscopy (fNIRS)] and electromyography of the respiratory muscles will be recorded.

#### 2.5.1. Pulmonary Function

All respiratory assessments will be conducted using the PowerLab C data acquisition system (ADInstruments, Bella Vista, Australia), ensuring standardized measurements across all tests. The system will be used in conjunction with specific accessories and calibrated according to the manufacturer’s instructions prior to each session.

Pulmonary function tests will be conducted during the baseline assessment to characterize the sample and as a secondary outcome to observe the effect of the applied intervention. Measures will be taken from flow–volume curves recorded in the seated position during standard spirometry. The technical procedures and equipment standardization will follow American Thoracic Society and European Respiratory Society (ATS/ERS) recommendations. Each individual will perform the test in a seated position on a comfortable chair using a nasal clip. Examiners will provide prior guidance on correctly performing the maneuver, which involves taking a maximum inspiration close to Total Lung Capacity (TLC) followed by a rapid, sustained expiration until the examiner signals to stop the maneuver.

During spirometry, the following variables will be assessed: Forced Vital Capacity (FVC), Forced Expiratory Volume in the first second (FEV1), Forced Expiratory Flow between 25 and 75% of the FVC curve (FEF25–75%), and the FEV1/FVC ratio. The assessment will be considered complete when three acceptable curves are obtained, with at least two being reproducible. The equipment used will be a spirometry extension. Daily calibration will be performed by injecting a 3000 mL volume of air through a syringe with a 3 L calibration pump. The values obtained will be compared to relative and absolute values for the Brazilian population [37].

The assessment of inspiratory and expiratory muscle strength will be obtained through maximum respiratory pressures (MIP and MEP, respectively) using a portable mouth pressure gauge connected to the PowerLab C system transducer (ADInstruments, Bella Vista, Australia), following the European Respiratory Society guidelines. Sitting in a chair with the backrest adjusted to 90° and the right arm supported, with the nostrils occluded by a nasal clip, the subject will be instructed to exhale to residual volume and then inhale with maximal effort for at least 1.5 s. A minimum of three reproducible and acceptable measurements will be performed; if the last maneuver is the highest, a new maneuver should be performed, and variability should not exceed 10% [38].

The nasal inspiratory pressure (SNIP test) will be performed with the participant in the same position as the previous tests. The subject will be asked, at the end of a quiet exhalation (functional residual capacity), to take maximum inhalation with one nostril occluded by a plug connected to a catheter attached to a manometer, while the other nostril remains free. The subject will perform a maneuver starting from functional residual capacity, with a closed mouth, taking a maximal “sniff” through the free nostril after a slow and relaxed exhalation. The maneuver is accepted when the maximum inspiration time is less than or equal to 0.5 s. Ten SNIP maneuvers will be conducted, each separated by a 30 s rest period [39].

The nasal expiratory pressure (SNEP) will be obtained under the same conditions as above, with the subject instructed, at the end of a quiet inhalation (total lung capacity), to perform a maximum exhalation using a nasal mask connected to a catheter attached to the manometer. The subject will be directed to perform a maneuver starting from total lung capacity, with the mouth closed, performing a forced exhalation through the nasal mask, preceded by a slow, deep inhalation. Ten SNEP maneuvers will be conducted, each separated by a 30 s rest period [40].

The maximum expiratory flow will be measured during a coughing maneuver, defining the peak expiratory flow (PEF). The PowerLabC system (ADInstruments, Bella Vista, Australia) equipped with a respiratory flow head will also be used to measure this.

Before each examination, subjects will be instructed on the procedures. Evaluators will demonstrate how the maneuver should be performed. The technical criteria for acceptability and reproducibility of maximum respiratory pressure tests will follow American Thoracic Society (ATS) and European Respiratory Society (ERS) guidelines. Initially, individuals will be asked to perform a learning maneuver, and the evaluation will be considered complete when there is less than a 10% variation between the two maximum values. Predicted values will be calculated using regression equations for calculating maximum pressures based on age and gender, as proposed for the Brazilian population [41,42].

#### 2.5.2. Surface Electromyography (sEMG) of Respiratory Muscles

Surface electromyography of the respiratory muscles will be used for acquiring and processing muscle depolarization data during respiratory curves, to characterize and quantify the recruitment level for each muscle during maneuvers. This will be conducted with 10 sEMG surface electrodes (Delsys Inc., Boston, MA, USA): 2 sensors placed on the scalene (ESC) muscles (5 cm from the sternoclavicular joint and 2 cm above this point), 2 sensors on the sternocleidomastoid (SCM) muscles (in the lower third of the distance between the mastoid process and the sternoclavicular joint), 2 sensors on the parasternal (PARA) muscles (in the second intercostal space, 3 cm from the sternum), and 4 sensors on the hemidiaphragms (H-DIA) (seventh and eighth intercostal space, one electrode between the costochondral junction and the midclavicular line, and another between the midclavicular line and the anterior axillary line). All sensors will be placed bilaterally to capture myoelectric data. Skin preparation will include trimming, cleaning with 70% alcohol, gentle abrasion with gauze, and electrode placement along muscle fiber orientation following the guidelines of the Surface Electromyography for the Non-Invasive Assessment of Muscles (SENIAM) [43] (Figure 4).

The selection of the scalene, sternocleidomastoid, parasternal, and hemidiaphragm muscles aims to capture the recruitment pattern of respiratory muscles under cortical control. Although the primary target of stimulation is the diaphragmatic motor cortex, its activation is not limited to the diaphragm and may also modulate accessory muscle activity during active breathing. Therefore, the selected muscle set provides a comprehensive assessment of the respiratory motor response induced by neuromodulation.

Sensors will be affixed to the skin using double-sided tape and transpore tape over the casing to minimize motion artifacts during the test. Signals are transmitted via Bluetooth through the EMGworks Acquisition software, version 4.8 (Delsys Inc., Boston, MA, USA) for standardized data acquisition and signal analysis. The sEMG signals will be processed using EMGWorks software version 4.8 for analysis, but for the evaluation of the diaphragm sensors will be used that allow for motor unit analysis through the Neuromap software, version 1.2.1 (Delsys Inc., Boston, MA, USA), accurately reporting the location of each motor unit according to a method that decomposes, synthesizes, and compares a physiological signal synthesized from the action potentials of the motor units obtained. The algorithm inspects the signal for clear and uncontaminated shapes of the motor units and then uses these shapes to identify all the firing locations of the motor units in the sEMG signal, including where the motor units overlap, allowing for the identification of the mean amplitude of the action potential, the firing threshold, and the maximum and average firing rates of the motor units [44,45,46].

Muscle electrical activity will also be monitored at rest (before maneuvers) and during recovery (after maneuvers). The highest values obtained from active MIP and MEP maneuvers will be used to normalize the electromyographic data based on peak analysis.

#### 2.5.3. Functional Near-Infrared Spectroscopy (fNIRS)

Functional Near-Infrared Spectroscopy (fNIRS) is a non-invasive neuroimaging technique that uses light in the near-infrared range, applying principles of absorption and scattering based on spatially resolved spectroscopy, to monitor brain activity by detecting local changes in blood oxygenation levels [47,48,49]. Hemodynamic changes in the diaphragmatic motor cortex (M1d) will be assessed during maximal respiratory activities using the Brite MKIII portable near-infrared brain imaging system (Artinis Corporation, Elst, the Netherlands). Measurements will be taken from 27 channels configured in 10 transmitters and 8 receivers mounted in a 3 × 7 grid attached to the participant’s head with an elastic band, with the central detector placed at Fz (10–20 system), and a 30 mm distance between each emitter and detector (Figure 5). Channels will be grouped to track perfusion in the diaphragmatic motor cortex. The OxySoft version 4.0 data acquisition and analysis software will be used for synchronized data collection. Light sources emit at 750 and 830 nm, and the sampling frequency will be set at 25 Hz. Average values of Oxy-Hb, Deoxy-Hb, and total hemoglobin concentrations in each channel will be assessed during rest and respiratory curve phases.

#### 2.5.4. Cortical Excitability—Transcranial Magnetic Stimulation (TMS)

Cortical excitability will be assessed using a Neuro-MS TMS device (Neurosoft Ltd., Ivanovo, Russia). MEPs will be recorded via surface electromyography (sEMG) from the hemidiaphragms, with activity captured using a NEURO-MEP amplifier (Neurosoft Ltd., Russia) with a 5 Hz low-pass filter and a 50 mV acquisition range. Stimulation will be non-invasively and painlessly administered with a Neuro-MS device connected to an “8”-shaped coil placed over the diaphragmatic motor cortex in the left hemisphere. The vertex and interaural and nasion–inion lines will be marked on a cap based on the 10/20 system, with a 1 × 1 cm grid drawn as a TMS reference [50,51].

The left primary motor cortex “hotspot” will be identified as the scalp location eliciting MEPs ≥ 50 μV in the respiratory muscles in at least 5 of 10 stimulations at the end of expiration, and during inspiration, respectively. For all TMS pulses, the “8”-shaped coil connected to a magnetic stimulator will initially target the primary diaphragmatic motor cortex, approximately 3 cm to the left of the midline and 2–3 cm anterior to the auricular plane [15,51]. The coil will be held by the operator and angled at 45° to the midline, with the handle pointing posteriorly, generating a posterior–anterior current flow in the brain during monophasic pulse delivery [52].

Surface EMG electrodes will be positioned bilaterally on the 7th and 8th intercostal spaces to monitor diaphragmatic motor responses [53,54]. TMS will be delivered at 80% of the maximum magnetic output at end-expiration, with participants in the sitting at 45° position. Diaphragmatic EMG will be continuously monitored to guide coil orientation, which will be adjusted around the stimulation hotspot to elicit the largest Motor Evoked Potentials (MEPs) during inspiration. Stimulation will be repeated five times at 45–60 s intervals, with the three highest-quality traces selected for analysis.

The cortical target will be identified and marked on the cap as the first grid location and explored in adjacent directions until optimal responses are obtained. To ensure accurate and consistent segmentation, the assessment will be processed using HD-Explore software (Soterix Medical, New York, NY, USA) for electric field modeling. The MRI image will be uploaded to the platform server, and the resulting individual model will be automatically integrated into the software for personalized anatomical mapping. Individual anatomical MRI scans will retrospectively confirm that stimulation was applied over the diaphragmatic motor cortex, located near the midline of the precentral gyrus, approximately 3 cm lateral to the vertex, as first described by Maskill et al. [51] and later investigated in studies on diaphragmatic corticospinal excitability in COPD and COVID-19 [15,55,56,57] (Figure 6). While absolute anatomical certainty is not achievable without combined TMS-fMRI, this protocol employs advanced neuronavigational procedures to maximize targeting accuracy.

After localization, the following will be evaluated: latency, amplitude, resting motor threshold (rMT), active motor threshold (aMT), corticospinal excitability, and cortical silent period (CSP). MEPs will be expressed as a percentage of average amplitude and analyzed for latency and area. Intracortical inhibition (SICI, LICI at 2 ms) and intracortical facilitation (SICF at 15 ms) will be assessed using 10 pulses (minimum 7) at 90% aMT [58,59,60].

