#### 1.1.2. Secondary Objectives

▪To assess cortical excitability by measuring patterns of facilitation, inhibition, active and resting motor thresholds, central motor conduction time, cortical silent period, and Motor Evoked Potentials (MEPs) in individuals with ALS;▪To evaluate cortical tissue perfusion in the region of the diaphragmatic primary motor cortex in individuals with ALS through specific respiratory tests before and after the HD-tDCS intervention protocol;▪To assess respiratory muscle electrical activity in individuals with ALS before and after the HD-tDCS intervention protocol;▪To observe the effects of HD-tDCS on aspects such as respiratory muscle strength, nasal inspiratory and expiratory pressures, and peak cough flow through specific respiratory tests in individuals with ALS;▪To observe the effects of HD-tDCS on clinical and functional aspects using the Amyotrophic Lateral Sclerosis Functional Rating Scale—Revised (ALSFRS-R);▪To assess motor control and muscle performance using a protocol for evaluating peripheral muscle electrical activity;▪To assess fatigue, dyspnea, pain, sleep, quality of life, and cognition before and after the HD-tDCS intervention protocol;▪To identify adverse effects of HD-tDCS on the diaphragmatic motor cortex in individuals with ALS.

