#### 2.6.2. Motor Control and Muscle Performance

The analysis of motor control and muscle performance will follow a protocol to assess muscle activity via surface electromyography (sEMG), using the TRIGNO™ Wireless System, Delsys Inc., based on the amplitude and frequency of the muscle’s electrical activity. The TRIGNO^TM^ consists of electrodes for surface electromyography collection, as well as inertial measurement units, including an accelerometer, gyroscope, and magnetometer. Sixteen wireless sensors will be used, each measuring 37 mm × 26 mm × 15 mm in a rectangular shape, with a sampling frequency of 1926 Hz for sensors number 1–12 and 1111 Hz for sensors number 13–16. The electrodes will consist of four pure silver contact bars, measuring 5 mm × 1 mm, with an inter-electrode distance of 10 mm. They will have a passband filter of 20–450 Hz, a capture range of 40 m, and an sEMG signal resolution of 16 bits [65].

The electrodes will be positioned perpendicular to the muscle fibers and fixed with double-sided adhesive. After hair removal and cleaning the area with alcohol, the sensors will be placed on the lower trapezius, anterior deltoid, biceps brachii (medial head), triceps brachii (lateral head), brachioradialis, long radial extensor of the wrist, short abductor of the thumb, and upper trapezius muscles, bilaterally [65]. The signal will be acquired over 25 s in three phases: initial rest (R1), activity (gestures and object handling), and final rest (R2). The acquisition during gestures (G) and object handling (M) activities will occur in two stages: pre-activity rest (5 s) and the execution of the activity itself (20 s) for each task. Bimanual tasks, such as gestures and object handling, will be performed first with the right upper limb, followed by the left upper limb. The selected tasks simulate those performed in daily living activities [65].

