**Figure 6 jcm-14-06701-f006:**
[figure not shown]
Schematic illustration of diaphragmatic motor cortex stimulation, referenced from point Cz according to the International 10–20 EEG electrode placement system. The diagram features a grid with 1 cm spacing used to identify regions of maximal muscle action potentials. A star symbol indicates various stimulation angles, while an arrow demonstrates the direction of the central current. The stimulation coil is represented at the bottom of the schematic, with an “X” denoting the aligned portion positioned over specific grid locations.

**Table 1 jcm-14-06701-t001:** Results, measurements, and analysis instruments according to objectives.

Outcome	Measures	Instrument
Cortical excitability	Latency and amplitude MEP—Motor Evoked Potential LMr—Rest Motor Threshold LMa—Active Motor Threshold CSP—Cortical Silent Period CMCT—Central Motor Conduction Time CIF—Intracortical Facilitation LICI—Long Interval Intracortical Inhibition SICI—Short Interval Intracortical Inhibition	TMS
Cerebral perfusion	HbDiff—Hemoglobin concentration difference at wavelength tHb—Total hemoglobin concentration at wavelength HHb—Deoxygenated hemoglobin concentration at wavelength O2Hb—Oxygenated hemoglobin concentration at wavelength TSI %—Tissue Saturation Index	f-NIRS
Respiratory muscular electrical activity	RMS (Root Mean Square)—Signal amplitude in microvolts Standardization of the signal in % RMS FM—Median Frequency Motor unit activation (recruitment) Neuronal firing Fatigue development	sEMG
Nasal pressures	SNIP—Maximum Inspiratory Nasal Pressure SNEP—Maximum Expiratory Nasal Pressure	PowerLab C
Cough peak flow	Maximum expiratory flow measured during a cough maneuver	PowerLab C
Functionality	Bulbar function—speech, salivation, swallowing; fine motor function—handwriting, food cutting, utensil handling; gross motor function—bed mobility, walking, stair climbing; respiratory function—breathing, orthopnea, respiratory failure	ALSFRS-R
Motor control and performance	Protocol for evaluating muscle activity through %RMS during rest, gestures, and object handling	sEMG
Fatigue	Nine statements, each item scored from 1 to 7, where 7 indicates maximum agreement with the statement	Fatigue Severity Scale
Fatigue/dyspnea	Scale from 0–10	Borg scale
Pain	Presence, intensity, and location of pain, with scores from 0 (no pain) to 10 (maximum pain) and body diagrams	Numerical Rating Scale (NRS) and Pain Body Drawings

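### Two TMS settings are wrong as written: a 5 Hz low-pass filter on the motor evoked potentials, and one 2 ms interval for both short- and long-interval inhibition

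*Protocol article*

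**What the plan says.** **Filter.** Section 2.5.4 takes the evoked potentials from surface electrodes over the hemidiaphragms, through an amplifier "with a 5 Hz low-pass filter and a 50 mV acquisition range". The hotspot is the site that gives responses of at least 50 microvolts "in the respiratory muscles in at least 5 of 10 stimulations at the end of expiration", and likewise during inspiration. The section then derives latency, amplitude, area, resting and active motor thresholds and the cortical silent period.

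The only other surface EMG band in the article is in Section 2.6.2, for a different device on upper-limb muscles: "They will have a passband filter of 20–450 Hz".

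**Intervals.** The same section states: "Intracortical inhibition (SICI, LICI at 2 ms) and intracortical facilitation (SICF at 15 ms". Table 1 has separate entries for short-interval inhibition and for "LICI—Long Interval Intracortical Inhibition". It calls the facilitation measure simply intracortical facilitation, whereas Figure 3 and the abbreviation list expand SICF as short-interval facilitation.

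**Conduction time.** The first secondary objective names "central motor conduction time, cortical silent period, and Motor Evoked Potentials (MEPs"), and Table 1 lists conduction time under TMS. The list of measures in Section 2.5.4 does not include it.

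**The concern.** A low-pass filter keeps what lies below its cut-off. A 5 Hz low-pass edge therefore keeps slow drift and suppresses a brief evoked response. The article's other EMG band, 20–450 Hz, lies wholly above 5 Hz.

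The hotspot search, the thresholds and the paired-pulse measures all start from this recording, at three centres. If the setting were applied literally at acquisition, the lost signal could not be recovered in analysis.

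The interval problem is a contradiction within the article. One 2 ms interval cannot define both a short- and a long-interval measure, so one Table 1 outcome would be a second copy of another under a different name. Data at an interval that was never stimulated cannot be supplied later.

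**Working it through.** **1. Filter gain**

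From the article: cut-off 5 Hz, low-pass; hotspot criterion 50 microvolts; other EMG band 20–450 Hz. The article gives no filter order, so Butterworth orders 1 to 4 are assumed. Gain at frequency f for order n is 1/√(1 + (f/5)^(2n)).

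| f | order 1 | order 2 | order 4 |
|---|---|---|---|
| 20 Hz | 24% | 6% | 0.4% |
| 50 Hz | 10% | 1% | 0.01% |
| 100 Hz | 5% | 0.25% | 0.001% |

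The first-order time constant is 1/(2π × 5) = 31.8 ms, as long as or longer than the responses assumed below. The silent period is read from ongoing EMG. If that EMG occupies 20–450 Hz, at most 24% of any component gets through.

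**2. Filtered evoked potential**

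The article gives no waveform, duration or amplitude. Assumed: 200 microvolts peak-to-peak, lasting 10, 15, 20 or 30 ms. The waves are one full sine cycle (biphasic) or a half sine (one-phase).

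| Wave | Order | Output, microvolts | Share kept |
|---|---|---|---|
| Biphasic | 1 | 10.6–33.3 | 5.3–16.6% |
| Biphasic | 2 | 1.6–11.5 | 0.8–5.8% |
| Biphasic | 4 | 0.65–5.8 | 0.3–2.9% |
| One-phase | 1 | 34.6–81.3 | 17–41% |
| One-phase | 2 | 19.0–55.9 | 9–28% |
| One-phase | 4 | 18.0–53.2 | 9–27% |

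For a biphasic response to show 50 microvolts at order 1, the true amplitude would have to be 50/0.166 ≈ 300 microvolts (30 ms) to 50/0.053 ≈ 940 microvolts (10 ms).

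Timing suffers too. For a smooth one-phase wave of 12 ms, the peak moves later by about 4 ms (order 1), 35 ms (order 2) or 92 ms (order 4).

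**3. The two likely intended settings**

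- 5 Hz as a *high-pass* edge: the biphasic wave keeps about 92–99.6% over orders 1 to 4. The half-sine wave overshoots to 108–132%.
- 5 *kHz* as a low-pass edge: both waves keep about 100%.

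Either would preserve the response. The article does not show which was meant.

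**4. Intervals side by side**

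| Measure | Section 2.5.4 | Name elsewhere |
|---|---|---|
| SICI | 2 ms | short-interval inhibition (Table 1) |
| LICI | 2 ms | long-interval inhibition (Table 1) |
| SICF | 15 ms | intracortical facilitation (Table 1); short-interval facilitation (Figure 3, abbreviations) |

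Reading the 2 ms as belonging to LICI alone does not help. The long interval would still be shorter than the 15 ms attached to a measure called short-interval.

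**The case against.** **A slip, likely to be caught.** The filter wording is most plausibly an error of filter type or unit. The Discussion says equipment is still being tested, and the Limitations promise a pilot of stimulation parameters and coil positioning. A literal 5 Hz low-pass would probably show there as grossly distorted traces. This stands as an argument against predicting lost data. It does not make the text right, and a centre working from it cannot tell which setting was meant.

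**No response would ever reach 50 microvolts.** A reader might infer this, and hence that thresholds could not be obtained. The documents do not support it, because they give no waveform, amplitude or filter order. A one-phase 200 microvolt response at order 1 still shows about 61 microvolts at 20 ms and 81 at 30 ms. A 30 ms biphasic response of about 300 microvolts reaches roughly 50. What holds across every case tried is heavy attenuation.

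**Ratios may survive.** A linear filter leaves the ratio of two identically shaped responses unchanged, so paired-pulse ratios suffer less in principle. They would still be formed from small residuals, and the absolute criterion and the latency are not protected.

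**Conduction time cannot be computed.** A reader might infer this from the lack of any described peripheral latency. That is silence in a condensed article, and the full protocol may hold the method. Only the mismatch between the objective, Table 1 and the Section 2.5.4 list is shown.

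**Half of the primary objective is lost.** That overreaches. The primary objective speaks of neurophysiological responses without naming TMS, and surface EMG and fNIRS also bear on it. Cortical excitability is itself the first secondary objective, which names inhibition but not LICI.

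**Conclusion.** Both stated settings are wrong as written and need correction before use.

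- **Filter:** about 0.3–17% of a biphasic response is kept, and up to about 41% of a one-phase response, with a delayed peak. These figures assume responses of 10–30 ms and a Butterworth filter of order 1 to 4. The exact loss depends on those assumptions; that most of the signal is lost does not. Measures derived from the evoked potential would be unreliable, which is a weaker claim than unobtainable.
- **Intervals:** LICI at 2 ms duplicates SICI and contradicts Table 1. This needs no assumption. The facilitation label is a lesser inconsistency.
- **Conduction time:** a minor mismatch between sections.

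**What to change.** Before the first TMS assessment:

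1. State the amplifier's filter type and both cut-offs so that the pass band contains the evoked potential. Examples are 5 Hz as the high-pass edge, or a low-pass edge in the kHz range. The sponsor should confirm which was intended and check the preset at all three centres.
2. Keep 2 ms for SICI only. Either give LICI its own long interval, or delete LICI from Section 2.5.4 and Table 1. The article gives no basis for a particular value, so the sponsor must supply it.
3. Use one name for the 15 ms facilitation measure in Section 2.5.4, Figure 3, Table 1 and the abbreviation list.
4. Reconcile conduction time: add it to the Section 2.5.4 measures with a pointer to its method, or remove it from the objective and Table 1.

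The cost is protocol wording and a check of amplifier and pulse-sequence presets. The sample size is unaffected. The only outcomes that could be lost are LICI and conduction time, and only if the sponsor chooses to drop them.
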